# Effectiveness of music therapy for alleviating pain during haemodialysis access cannulation for patients undergoing haemodialysis: a multi-facility, single-blind, randomised controlled trial

**DOI:** 10.1186/s13063-019-3773-x

**Published:** 2019-11-19

**Keywords:** Music therapy, Cannulation, Pain, Anxiety, Visual Analogue Scale, Haemodialysis

## Abstract

**Background:**

Repeated pain during haemodialysis access cannulations is a serious problem for haemodialysis patients even when prescribed oral or topical analgesics. Although some studies have observed the efficacy of music therapy for improving pain and anxiety, its effectiveness during haemodialysis access cannulations during dialysis is uncertain. The purpose of this study is to investigate the effects of music therapy for pain when cannulating haemodialysis access for haemodialysis patients.

**Methods:**

A prospective, multi-facility, single-blind, crossover, randomised controlled trial will be implemented. The intervention includes listening to Mozart, along with a white noise control condition. One hundred twenty haemodialysis patients will be enrolled across five facilities. Patients will be randomly allocated to either an Early-sequence group or a Later-sequence group. The Early-sequence group will receive cannulation while listening to Mozart’s Sonata for two pianos in D major (K.448) during the second week (Music period) and white noise during the fourth week (White noise period). The Later-sequence group will receive cannulation along with white noise first, followed by Mozart. All patients will also undergo cannulation during a no-sound period (wearing only headphones) during the first and third week (No-sound period). The music or no-music protocol will begin 8 min prior to the cannulating procedure, and participants will finish listening after starting haemodialysis during each period. The primary outcomes that will be assessed include the Visual Analogue Scale (VAS) score for pain during cannulation, and secondary outcomes are blood pressure, heart rate, VAS anxiety score, State-Trait Anxiety Inventory score, and salivary amylase activity. The operators who are in charge of haemodialysis access cannulation will be blind to the listening condition and VAS report.

**Discussion:**

The proposed study has several methodological benefits. First, using white noise is a suitable control condition for addressing the role of sound in pain management. Additionally, using a crossover design with repeated measurements can help control individual differences between participants, which should better distinguish between- and within-participant variability. Overall, music therapy is a safe and inexpensive intervention that does not have the problematic side effects typically associated with pharmacological treatment. If effective, music therapy can be easily implemented for reducing pain and anxiety during cannulation.

**Trial registration:**

This trial was prospectively registered to UMIN Clinical Trials Registry on 1 July 2018 (UMIN 000032850).

## Background

When kidney disease reaches its end stage, most patients undergo haemodialysis at least three times per week for life support. At the beginning of each session, two cannulations are required to be made. One is for removing blood from patients’ haemodialysis access, and the other is for returning blood to it. As such, patients often experience a significant amount of pain. This pain can be particularly problematic, especially given that many haemodialysis patients often undergo this procedure at least 150 times in a year [1–3]. Although several medications are available to alleviate this pain, 19.5% of haemodialysis patients experience severe pain [4]. Oral or topical analgesics are the most common treatment modality [5–7]. However, these medications can produce unwanted side effects (such as dermatitis); thus, they are not appropriate for all patients [8–12]. Moreover, aspects of cannulation pain cannot be easily reduced via oral or topical analgesics (i.e., feelings of anxiety or depression or both) [13–16]. However, certain sedatives or antidepressants, which may improve symptoms of anxiety or depression or both, can increase one’s risk of hypotension and physical dependence [17–20]. In addition, prescribing analgesics, sedatives or antidepressants can be expensive [21] and such expenses can be a serious issue for patients and insurers [22–24].

Given the aforementioned limitations of pharmacological treatment, the present study advocates the use of music therapy for pain management. Music therapy is safe and inexpensive and has been shown to improve pain and anxiety associated with several diseases [25–29]. In terms of cancer-related pain within a perioperative setting, music therapy helps alleviate pain, as noted by significant self-reported reductions in pain via Visual Analogue Scales (VASs) [30]. Music therapy is also effective for reducing lumbar puncture pain [31], and among haemodialysis patients, music therapy helps alleviate headaches, chest pain, and back pain resulting from disequilibrium syndrome [32]. Finally, music therapy has been effective for relieving pain during blood vessel cannulation procedures, given that such pain often derives from anxiety regarding the procedure [33–36]. However, no prior study has examined the effectiveness of music therapy on pain during haemodialysis access cannulations for haemodialysis patients.

The proposed study is a crossover, randomised controlled trial investigating the effectiveness of music therapy on pain during haemodialysis access cannulations administered to haemodialysis patients. Many previous studies assessing the effectiveness of music used only a no-sound control group [37], which could produce a potential ‘placebo effect’ for the intervention. For instance, music therapy effect sizes range from 26% to 58%, and the average effect is 35% [38, 39]. Given the placebo effect, the proposed study will use white noise as the control in order to better extract the true effect of music therapy.

## Methods/Design

Our main purpose for this trial is to clarify whether music therapy can truly alleviate pain, measured using a VAS metric, during cannulation into a haemodialysis access point, as compared with white noise. This protocol has been reported according to the Standard Protocol Items: Recommendations for Interventional Trials (SPIRIT) guidelines 2013 (see Additional file 1 for details).

### Design (Fig. 1)

This study will be a prospective, multi-facility, single-blind, crossover, randomised controlled trial. Haemodialysis patients will be allocated randomly and equally to either an Early-sequence or Later-sequence group. For the Early-sequence group, patients will receive cannulation while not listening to sound (only wearing headphones) during the first (run-in) week (No-sound period), listen to music during the second week (music period), listen to no-sound during the third (washout) week (No-sound period), and listen to white noise during the fourth week (White noise period). For the Later-sequence group, the no-sound period commences in the first (run-in) week, white noise during the second week, no-sound during the third (washout) week, and music during the fourth week.

**Fig. 1 Fig1:**
[figure not shown]
Trial workflow. There are four periods, one week each, for a total of four weeks

### Setting

This trial will be performed at five outpatient maintenance haemodialysis facilities: Jisyukai Ueda Kidney Clinic (Nagano, Japan), Nagasaki Renal Center (Nagasaki, Japan), Fujiidera Keijinkai Clinic (Osaka, Japan), Mihama Narita Clinic (Chiba, Japan), and Hakuyu Chiyoda Clinic (Osaka, Japan). The staff in all facilities will receive training on the trial method and protocol.

### Enrolment

Across the five facilities, patients over the age of 20 years who are undergoing outpatient haemodialysis three times a week, who have received dialysis for more than 6 months, and who indicated experiencing pain during cannulation based on a prior questionnaire will be enrolled. To evaluate the patients’ pain status, we will not adopt the VAS but rather a simple categorical scale questionnaire that will enable us to exclude patients who do not experience any pain (with a VAS of 0 mm) throughout the week of the intervention. The questionnaire is as follows:

Q-1) Do you feel pain when your haemodialysis access is cannulated?

Answer) A. Always; B. Sometimes; C. Never.

Q-2) Please answer Q-2 if you answered B on Q-1. About how often do you feel pain?

Answer) A. Once a week or more; B. Less than once a week.

Patients who answer A on Q-1, B on Q-1, and A on Q-2 are considered to have experienced pain and are eligible to participate. The use of analgesics is allowed throughout this trial.

#### Exclusion criteria

The exclusion criteria are as follows: not willing to participate; having a hearing, writing, or visual impairment; being paralysed; facing a difficulty communicating; having a psychiatric disorder or dementia; undergoing haemodialysis therapy fewer than three times per week; and receiving dialysis through an indwelling catheter.

### Trial interventions

The intervention for this protocol is referred to as ‘listening to sound’. The protocol will be performed while the patient is on a bed. The patient wears headphones (JVC HA - S 88 BN; JVC Kenwood Co., Kanagawa, Japan) connected to a tablet PC (BNT - 791 W.; Bluedot Co., Chiba, Japan). The sound will be provided by the Research Electronic Data Capture (REDCap) system (version 8.1.13; Vanderbilt University, Nashville, TN, USA) on a tablet PC. When the intervention is started, the participant will adjust the volume on the tablet PC screen. To reduce noise other than the sound from the headphones, we will use a noise-cancelling function. The specific intervention is outlined below (Fig. 2).

**Fig. 2 Fig2:**
[figure not shown]
Schematic diagram of intervention efficacy. The analgesic effects of music therapy are thought to include not only the true effect of music therapy but also two placebo effects (Headphones effect and Sound effect). Thus, music therapy will be set as the intervention, and white noise will be set as the control, in order to extract the true pain-alleviating effect of music therapy

#### Music

For this condition, patients will listen to music during cannulation. Mozart’s Sonata for two pianos in D major (K.448), which has been verified as the ‘Mozart effect’ in several studies [40–46], will be used. Eight minutes after listening to the piece, the operator will begin the puncture procedure (including disinfection, puncture, and blood removal). The patient will then finish listening to the piece after the punctures. There are two reasons for starting the music-listening period 8 min before the procedure. First, Sonata 2 major includes a first movement (‘Allegro con spirit D major 4/4 beat sonata form’), a second movement (‘Andante G major three quartz sonata form’), and a third movement (‘Molto allegro D major 2/4 of the beat Rondo Section’). At about the eighth minute, the song modulates from the first movement (with a fast tempo) to the second movement (with a slow tempo). Here, we expect that a relaxation effect could be expressed during the slow tempo of the second movement [37]. Second, in previous studies examining the Mozart effect, participants listen to the piece for 10 min [37]. During blood vessel cannulation for dialysis, two or more punctures are performed (removing and returning blood). Thus, in order to evaluate the most intense pain between punctures, it is difficult to set a strict timing. A previous study indicated that the puncture procedure takes about 4 min [47]. Therefore, we confirmed the actual puncture time needed in the pilot study. We observed that the puncture could be performed in about 10 min if the procedure began 8 min after the start of the piece; hence, the initial music period was set to 8 min. However, the timing can change when cannulation failure and other unforeseeable circumstances occur. There is a possibility that the effect of music therapy will vary depending on the listening time from music onset to cannulation. Therefore, we will record the time of the sound onset and the end of the intervention using REDCap. The occurrence of cannulation failure will also be recorded as conditional information regarding the cannulation. Hence, we will be able to perform sensitivity analyses using these data.

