Figure 3 shows the flow of the interventions performed each day during implementation. First, blood pressure (BP), heart rate (HR) and salivary amylase activity (S-AMY) will be measured. Then, the patient wears the headphones connected to the tablet PC. Eight minutes after the initial listening period (Music, White noise periods or No-sound), the operator will prepare for the haemodialysis access cannulation and then cannulate the haemodialysis access. Immediately after the cannulation, BP and HR will be measured again. After connecting the cannula to the haemodialysis machine, the patient will stop listening and report his or her VAS pain score, VAS anxiety score, and State-Trait Anxiety Inventory (STAI). Both the time from the start of listening to the sound and the time of the end of the intervention will be recorded by REDCap. The patients enter his or her VAS pain score, VAS anxiety score, and STAI directly into the REDCap system on a tablet PC. This procedure ensures data independence, as the operator and investigator will be blinded to patients’ reports. S-AMY is also measured at this time; however, S-AMY and STAI are assessed only during haemodialysis (HD)4, HD7, HD10 and HD13.

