**Fig. 3 Fig3:**
[figure not shown]
Data collection scheme. Each intervention will be performed for 8 min prior to starting the cannulation procedure to just after starting haemodialysis. *Will be measured only on HD4, HD7, HD10 and HD13

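### The recorded times give total listening time, not the onset-to-cannulation time that motivates the sensitivity analysis, so a true timing effect would be diluted unless puncture is time-stamped

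*Protocol article*

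**What the plan says.** The Music section of the protocol article justifies the lead-in at some length. The slow second movement begins at about the eighth minute, and "hence, the initial music period was set to 8 min". At that moment "the operator will begin the puncture procedure (including disinfection, puncture, and blood removal"), so even the start of the procedure is not the first needle insertion.

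The section then allows that "the effect of music therapy will vary depending on the listening time from music onset to cannulation", and draws the consequence that "we will record the time of the sound onset and the end of the intervention using REDCap". The next sentence adds that cannulation failure is recorded too, and the section concludes that these data will support sensitivity analyses. It fixes no model and no exposure variable.

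The Study protocol section names the same two times: "Both the time from the start of listening to the sound and the time of the end of the intervention will be recorded by REDCap". It also places the end: "After connecting the cannula to the haemodialysis machine, the patient will stop listening and report his or her VAS pain score". The legend of Fig. 3 agrees: "Each intervention will be performed for 8 min prior to starting the cannulation procedure to just after starting haemodialysis".

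The per-session list under Conditional information includes the number of cannulations but no puncture time. Table 1 adds no time variable. The Monitoring section describes the REDCap log as holding input time and listening time.

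**The concern.** The interval said to matter runs from sound onset to cannulation. The interval that can be computed runs from sound onset to a moment after cannulation, connection and the start of dialysis. The second contains the first plus the whole puncture phase, and the two recorded times cannot separate them.

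The extra part is not neutral noise. The Music section itself says failure shifts the timing. Under Primary outcomes, the score is the maximum pain over all cannulations in the session, and a maximum over more punctures can stay the same or rise but cannot fall. Total listening time is therefore partly a marker of a difficult cannulation.

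At stake is how the timing analysis can be read, and whether the intended lead-in can be verified at puncture. With the listed data, neither the listening time before the needle nor the position in the piece at that moment can be checked.

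**Working it through.** The plan states no figure on this point, so there is none to reproduce. The check is one of identification, followed by an illustration of size.

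**Identification.** Write

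T = A + B,

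where T is end minus onset (recorded), A is onset to first puncture (the interval of interest) and B is first puncture to end. Only T is observed, so A cannot be recovered from it.

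**Illustration: inputs.** All are assumptions except where noted.
- A: SD 1.5 min, variance 2.25.
- B without failure: mean 4 min (the Music section cites about 4 min for the puncture procedure), assumed SD 1 min, variance 1.
- Failure probability p: 5%, 10% or 15% of sessions. Each failure adds m = 4 min and d = 5, 10 or 15 mm to the maximum pain score. The protocol does not state that failed punctures hurt more; d is an assumption.
- b: true slope of pain on A, either 0 or -0.5 mm/min.
- A, B and failure are taken as independent.

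**1. Music sessions only, failure ignored.** The expected slope of pain on T is

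[b × 2.25 + m × d × p(1 − p)] / [2.25 + 1 + m² × p(1 − p)].

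- b = 0, p = 5%, d = 5: (4 × 5 × 0.0475) / (3.25 + 16 × 0.0475) = 0.95 / 4.01 = +0.24 mm/min.
- b = 0, p = 15%, d = 15: (4 × 15 × 0.1275) / (3.25 + 16 × 0.1275) = 7.65 / 5.29 = +1.45.
- b = -0.5, p = 10%, d = 10: (-1.125 + 3.60) / (3.25 + 1.44) = 2.475 / 4.69 = +0.53.
- b = -0.5 over all nine combinations: -0.04 to +1.23, with the wrong sign in eight of nine.

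**2. Same sessions, adjusted for recorded failure (or restricted to sessions without it).** The slope is b × 2.25 / (2.25 + 1).

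- b = 0: 0.
- b = -0.5: -0.5 × 0.692 = -0.35.
- If the SD of B is 2 min instead of 1: -0.5 × 2.25 / (2.25 + 4) = -0.18.

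**3. Difference in slopes, music minus white noise, failure ignored.** If failure acts equally in both conditions, its term cancels and the difference is b × 2.25 / [2.25 + 1 + m² × p(1 − p)].

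- b = 0: 0.
- b = -0.5: -1.125 / 4.01 = -0.28 at p = 5%, and -1.125 / 5.29 = -0.21 at p = 15%. The sign is right in all nine combinations.

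**4. Other assumed inputs.** A simulation used SD of A 1 min, SD of B 1 or 2 min, failure in 5% or 10% of sessions, a failure adding 3 or 5 min and 5 or 15 mm, and residual SD 12 mm (the pilot SD in the Sample size section). Results, in mm/min:

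| True slope | Total time, failure ignored | Adjusted for failure |
|---|---|---|
| 0 | +0.14 to +1.60 | -0.03 to +0.01 |
| -1.0 | -0.12 to +1.34 | -0.53 to -0.19 |

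The correlation of T with A was 0.37 to 0.64. Adjustment removes the spurious slope and leaves the true one diluted by about half to four fifths, in line with 1/(1 + 1) = 0.5 and 1/(1 + 4) = 0.2 from the formula in step 2.

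**The case against.** A reader might infer that the sensitivity analysis cannot be run because two times are all that is recorded. The protocol does not support that. Failure is recorded, as the sentence after the one on recorded times says, and the number of cannulations is on the per-session list. The promise is of analyses using all of these data, so an analysis of total listening time that handles failure is feasible.

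A reader might also infer that the planned analysis will hide or reverse a real benefit of listening before puncture. That needs a music-only model that leaves out a variable the authors say they collect for this purpose, and the protocol specifies no such model. The trial's contrast is music against white noise, with the same procedure and an operator who does not know which sound is playing. In that contrast a failure effect common to both conditions cancels.

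Two further objections carry weight. The size of any bias rests on assumed inputs. And because the maximum over two or more punctures is scored, time to the first puncture is not always listening time at the moment scored.

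What remains is that the protocol names one interval, gives recording two times as its response, and those times do not yield that interval. This is a statement in the text, not detail left to an analysis plan. Handling failure does not cure the dilution, and its size cannot be estimated from the listed data. Fig. 3 is not shown, and log times might allow a rough reconstruction, but the text does not say so.

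**Conclusion.** The point holds as a mismatch between the stated motive and the recorded data. Total listening time is a post-puncture proxy for onset-to-cannulation time. With failure handled, the expected harm is dilution: under the assumed inputs a true -0.5 mm/min appears as about -0.35, or about -0.18 if the puncture phase has an SD of 2 min. A null result would then say little about lead-in time. Sign reversal is confined to a music-only analysis that ignores failure.

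These sizes depend on assumed failure rates, added minutes, added pain and timing SDs. The mismatch itself depends on none of them. The primary comparison does not use listening time, so its estimate, power and error rate are unchanged. This is a minor point about a sensitivity analysis.

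**What to change.** For remaining sessions, add a REDCap time stamp at first needle insertion and, since maximum pain is scored, ideally another at the last insertion. Define listening time for the sensitivity analysis as sound onset to puncture.

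For sessions without the stamp, amend the text before analysis:
- call the exposure total listening time;
- restrict to sessions without a failed puncture, or adjust for failure;
- test it as an interaction with condition (music versus white noise);
- state that it is not to be read as onset-to-cannulation time.

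The cost is one extra tap per session for each stamp, on the tablet already in use, and a few sentences of text. The main limit is timing. The Trial status section reports 102 participants already randomised of 120 planned (85%), with recruitment due to end in September 2019, so the stamp would reach at most the remaining 18 in full, and perhaps none. The relabelled analysis that takes failure into account is therefore the main usable remedy for this trial.

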#### White noise

During the white-noise period, the patient will listen to white noise during cannulation [48]. White noise is defined as sound comprising the same intensity of all frequencies within the range of human audition (1–22.05 KHz) [30, 49]. (The sound can be heard in https://www.youtube.com/watch?v=_CMzWGteDCY.) White noise has no orderly arrangement regarding melody, harmony, rhythm, tone or pitch, which is required for a sound to be considered musical [50, 51]. White noise was chosen as a control condition to isolate the effect of wearing headphones (Headphones effect) and the effect of stimulating hearing with sound (Sound effect).

#### No-sound

The no-sound period includes attaching headphones with no sound present. Outer noise is still cancelled out by the headphones [52]. This intervention will be used during the run-in and washout periods. During this period, we will attempt to diminish the placebo effect by using headphones.

### Study protocol

Figure 1 outlines the trial protocol and randomisation procedure. The intervention will be performed during each study period from the time of cannulation to the start of dialysis (thrice a week) (Table 1).

**Table 1 Tab1:** Summary of collected data at each time point according to SPIRIT 2013 guideline

TIME POINT	Enrolment HD1	1 week			1 week			1 week			1 week		
		HD2	HD3	HD4	HD5	HD6	HD7	HD8	HD9	HD10	HD11	HD12	HD13
ENROLMENT													
Eligibility screening	×												
Informed consent	×												
Allocation	×												
INTERVENTIONS													
Early-sequence													
No-sound		×	×	×				×	×	×			
Music					×	×	×						
White noise											×	×	×
Later-sequence													
No-sound		×	×	×				×	×	×			
Music											×	×	×
White noise					×	×	×						
ASSESSMENTS													
Baseline information	×												
VAS pain score		×	×	×	×	×	×	×	×	×	×	×	×
VAS anxiety score		×	×	×	×	×	×	×	×	×	×	×	×
STAI Y-1				×			×			×			×
STAI Y-2	×												
BP and HR		×	×	×	×	×	×	×	×	×	×	×	×
S-AMY				×			×			×			×
Conditional information		×	×	×	×	×	×	×	×	×	×	×	×
Adverse events		×	×	×	×	×	×	×	×	×	×	×	×

*Abbreviations*: *BP* blood pressure, *HD* haemodialysis, *HR* heart rate, *S-AMY* salivary amylase activity, *SPIRIT* Standard Protocol Items: Recommendations for Interventional Trials, *STAI* State-Trait Anxiety Inventory, *VAS* Visual Analogue Scale

Figure 3 shows the flow of the interventions performed each day during implementation. First, blood pressure (BP), heart rate (HR) and salivary amylase activity (S-AMY) will be measured. Then, the patient wears the headphones connected to the tablet PC. Eight minutes after the initial listening period (Music, White noise periods or No-sound), the operator will prepare for the haemodialysis access cannulation and then cannulate the haemodialysis access. Immediately after the cannulation, BP and HR will be measured again. After connecting the cannula to the haemodialysis machine, the patient will stop listening and report his or her VAS pain score, VAS anxiety score, and State-Trait Anxiety Inventory (STAI). Both the time from the start of listening to the sound and the time of the end of the intervention will be recorded by REDCap. The patients enter his or her VAS pain score, VAS anxiety score, and STAI directly into the REDCap system on a tablet PC. This procedure ensures data independence, as the operator and investigator will be blinded to patients’ reports. S-AMY is also measured at this time; however, S-AMY and STAI are assessed only during haemodialysis (HD)4, HD7, HD10 and HD13.

